#### Data gathering

Data are collected in the intervention group and control group in identical ways. Outpatient surgery is performed on a weekly basis, therefore hospital charts will be reviewed weekly. The study has been approved by the Norwegian Data Inspectorate. All data will be handled with strict confidentiality, and study reports or presentations will maintain the anonymity of patients, surgeons, GPs and hospitals. Data collection will be complete by the end of 2009.

#### Analysis

Treatment arms will be compared with respect to potential covariates using continuous and categorical variables. This will include variables related to patients (sex, age, type of disease, date of referral, date of outpatient examination, date of outpatient surgery), cost (patient sick leave, GP examination, hospital administration, surgical outpatient examination, surgical outpatient treatment, unused surgical capacity due to incorrect referral, patient travel cost). The results will be presented as intention-to-treat analyses and treatment analyses.

We will conduct analyses using the latest version of SPSS. The trial will be reported according to the CONSORT standards for reporting randomised trials [6,7].

The results will be expressed as an odds ratio (for binary outcomes), hazard ratio (time to event outcomes) or mean difference (for continuous outcomes) with corresponding standard errors, 95% confidence intervals and associated p-values. For all two-sided tests we use alpha = 0.05 level of significance.

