**Materials and Methods:**

In a randomised controlled trial, selected patients (inguinal hernia, gallstone disease and pilonidal sinus) referred to the university hospital are either randomised to direct electronic referral and booking for outpatient surgery (one stop), or to the traditional patient pathway where all patients are seen at the outpatient clinic several weeks ahead of surgery.

Consultants in gastrointestinal surgery designed standardised referral forms and guidelines. New software has been designed making it possible to implement referral forms, guidelines and patient information in the GP's electronic health record. For "one-stop" referral, GPs must provide mandatory information about the specific condition. Referrals were linked to a booking system, enabling the GPs to book the hospital, day and time for outpatient surgery. The primary endpoints are waiting time and costs. The sample size calculation was based on waiting time. A reduction in waiting time of 60 days (effect size), 25%, is significant, resulting in a sample size of 120 patients in total.

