#### Outcome measures

##### Primary outcome

##### Waiting time for outpatient surgery

This time interval will be calculated retrospectively and compared between the two groups. The waiting time specified by health authorities is unreliable (Table 1); waiting time must therefore be calculated separately for each individual using dates from the electronic health record. This will consist of the following dates: the date the referral is noted in the hospital electronic health record, the date of outpatient examination (for the control group) and the date of outpatient surgery.

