##### Sample size

To calculate the sample size needed, we identified all patients who had undergone the specified surgical procedures within three months of normal surgical activity (September, October and November 2007). Of these 33 patients, 22 patients could be included in a one-stop protocol. The rest of the patients were not eligible due to different patient pathways.

We calculated the average waiting time from referral to examination at the surgical outpatient dept, the waiting time from outpatient examination to surgery, and the total waiting time (Table 2).

**Table 2 T2:** Mean waiting time for examination and surgical treatment for selected day case prcedures at a University Hospital during a three-month period of normal activity.

	GP referral to examination at the surgical outpatient clinic (days)	Internal hospital referral to day case surgery (days)	Total waiting time (days)
Waiting time^a ^(mean)	122	119	241
Standard deviation	118	92	154

^a ^Inguinal hernia, pilonidal sinus and uncomplicated gallstone disease

Based upon calculations in Table 2, we assume that there is no significant difference in waiting time between the three groups. Alpha and beta were set at 0.05 and 0.2 respectively. We estimate that a significant decrease in mean waiting time for surgery would be 60 days. The standard deviation is estimated as 120 days. We assume an exclusion rate of 20%, so that a sample size of 60 patients in each group is required.

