#### Randomisation

Patients will be randomised at the time of referral by the GP. The randomization service is telephone-based and managed by the University Hospital. Patients are stratified into three groups according to their diagnosis.

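### Diagnosis stratifies the randomisation but has no stated role in the effect estimate, and it shares one covariate list with components of both primary endpoints

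*Protocol article*

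**What the plan says.** The Randomisation section states: "Patients are stratified into three groups according to their diagnosis". The Analysis section states: "Treatment arms will be compared with respect to potential covariates using continuous and categorical variables". The patient variables it then names are "sex, age, type of disease, date of referral, date of outpatient examination, date of outpatient surgery". The cost variables begin with sick leave, GP examination and hospital administration, and continue with "surgical outpatient examination, surgical outpatient treatment, unused surgical capacity due to incorrect referral, patient travel cost". Results are to be expressed as an odds ratio, hazard ratio or mean difference according to the type of outcome. No sentence says which covariates, if any, enter the estimate.

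The same dates and costs appear elsewhere as outcomes. The section on waiting time builds the outcome from "the date the referral is noted in the hospital electronic health record, the date of outpatient examination (for the control group) and the date of" the operation. The abstract says: "The primary endpoints are waiting time and costs". The cost-minimisation section has costs estimated and compared between the groups.

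Under Sample size, citing Table 2, the authors write that "we assume that there is no significant difference in waiting time between the three groups".

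**The concern.** Two things are unclear, and one stated assumption lacks support.

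- **Role of diagnosis.** Once randomisation is stratified, diagnosis is balanced between arms by design. If it also predicts waiting time, an analysis that leaves it out uses too large a standard error. The test is then conservative and may lose power.
- **Content of the covariate list.** Sex, age, diagnosis and referral date describe the patient at entry. Examination date, surgery date and most cost items arise later and make up the primary endpoints. If an analyst took the label literally and adjusted for them, the treatment effect would shrink or disappear. The examination date also exists only in the control pathway, so it cannot serve as a covariate across both arms.
- **Assumption of no difference between diagnoses.** Table 2 gives one pooled mean and SD for all three conditions together, from 22 patients. It has no figure by diagnosis, so the assumption cannot be drawn from it.

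**Working it through.** **The plan's own figure.** Inputs from Sample size: difference 60 days, SD 120 days, alpha 0.05, power 80%, exclusions 20%, 60 per group. The Analysis section refers to two-sided tests.

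- Two-sided: n = 2(1.96 + 0.842)² × (120/60)² = 62.8, so 63 evaluable per group. With exclusions, 63/0.8 = 78.75, so 79.
- One-sided: n = 2(1.645 + 0.842)² × 4 = 49.5, so 50. Then 50 × 1.2 = 60.

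The stated 60 is therefore matched only by a one-sided test with exclusions added as n × 1.2. That is a separate matter. It enters here only because 60 × 0.8 = 48 evaluable per group, on which the rest is based.

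**Cost of leaving diagnosis out.** Let R² be the share of waiting-time variance explained by diagnosis. The document gives no value, so a range is assumed. The arms are taken as balanced within each diagnosis, and total SD is held at 120.

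- Unadjusted standard error: 120 × √(2/48) = 24.49 days.
- Adjusted standard error: 24.49 × √(1 − R²).
- Adjusted power: Φ(60 / adjusted SE − 1.96).
- Unadjusted power: Φ((60/24.49 − 1.96) / √(1 − R²)). The test uses the larger SE, while the estimate varies with the smaller one.
- Unadjusted type I error: 2 × [1 − Φ(1.96 / √(1 − R²))].

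| Assumed R² | Power, adjusted | Power, unadjusted | Loss (points) | Type I error, unadjusted |
|---|---|---|---|---|
| 0 | 68.8% | 68.8% | 0 | 5.0% |
| 0.05 | 71.0% | 69.2% | about 2 | 4.4% |
| 0.10 | 73.3% | 69.7% | about 4 | 3.9% |
| 0.20 | 78.2% | 70.8% | about 7 | 2.8% |

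For scale, take three equal strata with means at −d, 0 and +d days. Then R² = (2d²/3)/120², which is 0.02 for d = 20, 0.07 for d = 40 and 0.17 for d = 60. A share near 0.20 thus needs diagnoses more than 120 days apart from lowest to highest mean.

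**What adjustment for the listed dates would do.** Waiting time W = surgery date − referral date. If both dates are in the model, W is an exact linear function of the covariates and nothing is left for treatment to explain. A simulation of 2,000 trials shows the size. It used 48 per arm, mean waits of 241 and 181 days (a true effect of −60), SD 120, gamma-distributed waits and referral dates spread evenly over one year. The last two are assumptions.

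- No adjustment: −60.6 days.
- Adjusted for surgery date: −27.5 days.
- Adjusted for surgery and referral date: 0.0 days.

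The zero is an identity and does not depend on the assumptions. The −27.5 does.

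**The case against.** A reader might infer that the analysis discards the strata. The text does not show that: diagnosis is in the covariate list, under type of disease. What is unstated is its role in the estimate, and a full protocol or SAP that is not shown may settle this.

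A reader might also infer that adjustment for the outcome is planned. The Analysis section says only that the arms are compared on these variables, and other sections already treat the dates and costs as outcomes. This part of the objection stands. The fault is a wrong label with a possible bad consequence.

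Nor does the article use the no-difference assumption to justify an unadjusted analysis. The sentence is a sample-size assumption, and the point against it is only that Table 2 cannot support it.

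Table 1 might seem to prove that diagnoses differ, since the longest surgery wait is 48 weeks for pilonidal sinus against 28 and 30 for the others. But the minimum is 2 weeks for all three, and the section on waiting time calls these figures unreliable. They make a difference plausible and no more.

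Finally, one-stop booking shows slots over a 6-month period, which may compress differences between diagnoses in that arm. That argues for the lower part of the R² range. None of this removes the mixed list or the missing role of the stratifier.

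**Conclusion.** The point holds in a limited form. The firmest part needs no assumption: the article places components of both primary endpoints under the label of covariates, and a model using referral and surgery dates together would return zero whatever the true effect.

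The part about diagnosis is one of efficiency. The loss is nil under the protocol's own assumption and reaches about 7 power points only at an assumed 20% of variance. It rests on 48 evaluable patients per arm, a total SD of 120 days, balance within strata and R² values that the document does not supply. The error is in the conservative direction. Actual loss of precision is possible but not shown. The change is still worth making, because it is nearly free and adjusted power at 48 per arm stays below the planned 80% throughout this range.

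**What to change.** In the Analysis section:

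1. State that the primary waiting-time and cost comparisons are adjusted for, or stratified by, diagnosis.
2. Restrict covariates to variables fixed before randomisation: diagnosis, age, sex and referral date. Since patients are randomised at referral, the referral date is best taken as the date of randomisation.
3. Move examination date, surgery date and the cost items to the list of outcomes. Note that the examination date applies to the control pathway only.

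In Sample size, present the absence of a difference between diagnoses as a plain assumption, or give the waiting times by diagnosis; do not attribute it to Table 2.

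The cost is wording and two degrees of freedom for three diagnoses. If diagnosis turns out not to be prognostic, nothing material is lost.

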## Abstract

**Background:**

Waiting time and costs from referral to day case outpatient surgery are at an unacceptably high level. The waiting time in Norway averages 240 days for common surgical conditions. Furthermore, in North Norway the population is scattered throughout a large geographic area, making the cost of travel to a specialist examination before surgery considerable. Electronic standardised referrals and booking of day case outpatient surgery by GPs are possible through the National Health Network, which links all health care providers in an electronic network. New ways of using this network might reduce the waiting time and cost of outpatient day case surgery.

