##### Cost-minimisation analysis

We will use a cost-minimisation analysis in this study, since this health care intervention has a similar medical outcome for both groups, i.e. surgical outpatient treatment [5]. The analysis will have a public health provider perspective. This includes travel costs, since the public health service pays for these costs in Norway. Direct health care costs that are the same in both alternatives will be excluded. The costs for the GPs providing this service will include investment, support, and time costs. Costs of traditional referral will include hospital administration, examination at the Surgical Outpatient Department (surgeon time, nurse time), surgical treatment at the Department of Day Case Surgery (surgeon time, anaesthetist time, and nurse time) unused surgical capacity due to incorrect referral, and patient travel costs. All costs will be estimated separately and compared between the two groups.

We will then conduct a threshold analysis. This analysis calculates the number of patients needed to break even, i.e. where the cost of providing a one-stop service equals the cost of traditional referrals.

This value is given by:

Total cost of one-stop service = Total cost of traditional referral

F_OS _+ xV_OS _= F_TR _+ xV_TR_

X = (F_OS _+ F_TR_)/(V_OS _- V_TR_)

X = number of consultations; F = fixed costs; V = variable costs; OS = one-stop; TR = traditional referral;

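### The covariate list mixes baseline variables with components of both primary outcomes and names no baseline travel measure; for cost this is a matter of precision, not bias

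*Protocol article*

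**What the plan says.** All references are to the protocol article.

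- Abstract, Materials and Methods: "The primary endpoints are waiting time and costs", and "The sample size calculation was based on waiting time".
- Analysis: the arms are to be compared on potential covariates. "This will include variables related to patients (sex, age, type of disease, date of referral, date of outpatient examination, date of outpatient surgery), cost" is followed by a bracket of cost items: sick leave, GP examination, administration, clinic examination, surgical treatment, capacity lost to wrong referrals, and travel. No regression or adjusted model is described. Continuous outcomes are reported as a mean difference with a 95% confidence interval.
- Cost-minimisation analysis, on the perspective of the costing: "This includes travel costs, since the public health service pays for these costs in Norway". Direct costs that are equal in both arms are left out.
- Abstract, Background: "in North Norway the population is scattered throughout a large geographic area, making the cost of travel to a specialist examination before surgery considerable".
- Randomisation: "Patients are stratified into three groups according to their diagnosis".

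**The concern.** Two things stand out in the list.

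First, it puts variables known at allocation together with variables that the intervention is meant to change. Taken literally as a set of adjustment covariates, it would have the analyst condition on parts of the outcome. For cost, that would remove the very saving the trial wants to measure.

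Second, the one baseline quantity that the article's own rationale points to, how costly it is for a patient to travel, is absent. Control patients visit the clinic and, if surgery is indicated, return for it; one-stop patients go straight to surgery. Travel cost per patient is then roughly the number of trips times a trip cost set largely by where the patient lives. Diagnosis-only stratification does nothing to balance this, and cost has no sample size of its own. A baseline travel value could therefore buy precision on a primary endpoint whose precision was not planned.

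**Working it through.** **1. Sorting the list.**

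| Item in the Analysis section | Status |
|---|---|
| Sex, age, disease, referral date | Known at allocation (patients are randomised at referral) |
| Examination date, surgery date | After allocation; used to compute waiting time (Outcome measures) |
| Travel and the other cost items | After allocation; cost items compared as outcomes |
| Home location or standard travel cost | Not listed |

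**2. What conditioning on travel cost would do.** Write cost = travel + other costs. Assume a travel saving of 1 unit and a non-travel saving of 0.5 unit, so the true saving is 1.5. With realised travel cost in the model, the arm coefficient estimates only the non-travel part, 0.5. The share lost is 1/1.5 = 67%. A simulation under this assumption gave 66.5% to 67.0%.

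**3. Number of patients.** The plan has no figure for cost to reproduce. Its only sample size, 60 per group, is for waiting time. A two-sided calculation at alpha 0.05 and 80% power gives 2 × (1.96 + 0.84)² × 120²/60² = 63 per group before loss and 63/0.8 = 79 after, so 60 is not reproduced that way. That is a separate matter; here 60 serves only as a count. With 20% exclusions, 60 × 0.8 = 48 per arm.

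**4. Precision of the cost difference.** No cost amounts, SDs or travel share are given, so these inputs are assumptions. The unit is one mean return trip; controls make 2 trips and one-stop patients 1; CV is the between-patient coefficient of variation of trip cost; s is the SD of all other costs; n is per arm.

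- Unadjusted variance: (4·CV² + s²)/n + (CV² + s²)/n = (5·CV² + 2s²)/n.
- Adjusted variance (centred trip cost with arm interaction): 2s²/n + CV²/(2n).

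At n = 48:

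| CV, s | Unadjusted SE | Adjusted SE | Ratio |
|---|---|---|---|
| 0.5, 2 | √(9.25/48) = 0.44 | √(8/48 + 0.25/96) = 0.41 | 0.94 |
| 1, 1 | √(7/48) = 0.38 | √(2/48 + 1/96) = 0.23 | 0.60 |
| 1.5, 0.5 | √(11.75/48) = 0.49 | √(0.5/48 + 2.25/96) = 0.18 | 0.37 |

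Put differently, let p be the share of within-arm cost variance due to distance. The variance falls by the fraction 4.5/(5/p) = 0.9p, so the SE ratio is √(1 − 0.9p): 0.95 at p = 10%, 0.88 at 25%, 0.74 at 50%, 0.57 at 75% and 0.44 at 90%.

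**5. If the surgery trip is dropped as common to both arms.** Controls then carry 1 trip and one-stop patients 0. At CV 1, s 1, n = 48 the unadjusted SE is √(3/48) = 0.25, the adjusted SE is again 0.23, and the ratio is 0.91.

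**6. Is there bias?** In 4000 simulated trials per setting at 60 per arm, with CV 0.5 or 1 and p of 25%, 50% or 90%, the unadjusted difference centred on the true value and its 95% interval covered it in 94.4% to 95.3% of runs.

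**7. Size of chance imbalance.** With a mean of 1.5 trips, imbalance in distance alone has a 95% range of ±1.96 × 1.5 × CV × √(2/48). That is ±0.60 trip at CV 1 and ±0.90 at CV 1.5, against a travel saving of 1 trip.

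**The case against.** The strongest reply is that the Analysis section never says cost will be adjusted for these items. It says the arms are compared on them, travel sits in the cost bracket, and the cost-minimisation section says the costs are to be compared between groups. On that reading travel cost is simply an outcome component, and the loss in step 2 never occurs. It is also fair that adjustment covariates are commonly left to an analysis plan, which is not shown, and that an unadjusted randomised comparison is valid.

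Much of this stands. The harm from conditioning on travel cost arises only if it enters a model, and the absence of a distance variable alone would be a weak point. What remains is that the article does fix a list, calls its members potential covariates, and includes outcomes among them. That leaves the use of the list open and needs correcting.

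A reader might also infer more than the article supports:

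- That distance drives cost, or that much precision is lost. Travel is called considerable, but GP investment and time, administration, staff time and unused capacity are costed too, and no amounts are given.
- That chance imbalance biases the comparison. It does not; it is already in the unadjusted confidence interval.
- That imbalance in distance could reverse the saving. In neither case in step 7 does its 95% range reach the 1-trip saving.

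Finally, the trip counts are idealised. Some controls may not be referred on to surgery, and some one-stop referrals may be wrong. The calculation adjusts for the exact trip cost, whereas a nearest-site value is a proxy, so the gains shown are upper bounds.

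**Conclusion.** The point holds as a correction of the covariate list plus an assumption-dependent gain in precision. The firm part needs no arithmetic: cost items and the examination and surgery dates are outcomes or parts of outcomes and must not be adjustment covariates.

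The second part is conditional. Adjusting the cost difference for baseline travel multiplies its standard error by about 0.95 if distance explains 10% of within-arm cost variance, and by about 0.4 at the favourable extreme. The middle case is 0.60 with both trips counted and about 0.9 if the surgery trip is excluded. A large gain needs distance to explain roughly half or more of the variance, which the article neither shows nor rules out. The unadjusted analysis remains unbiased with nominal coverage.

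**What to change.** In the Analysis section:

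1. Split the list into baseline covariates (sex, age, diagnosis, referral date) and outcomes (all cost items, and the examination and surgery dates), and state that only the first group may be used for adjustment.
2. Add one baseline covariate: a standard return-travel cost from the patient's home to the nearest of the three hospital sites, fixed at randomisation. It must not depend on the hospital later used, because one-stop patients choose theirs after allocation.
3. Report the difference in cost per randomised patient adjusted for this value and diagnosis, with robust standard errors. If an arm-by-travel interaction is included, centre the travel value and average the arm difference over all randomised patients.
4. Keep the unadjusted difference as a sensitivity analysis.

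The cost is one derived variable per patient, probably obtainable from data that travel costing needs anyway, and slightly more analysis work. No patients or visits are added.

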##### Intervention

The one-stop strategy is a set of interventions directed at GPs referring patients to the University Hospital. The interventions include: Guidelines for referral, standardised electronic referrals, booking for outpatient surgery and a patient information form.

Guidelines for referral: Guidelines for inguinal hernia, sinus pilonoidalis and gallstone disease were developed (Figure 3). All surgeons performing the surgical procedures reviewed the giudelines, and after a three-month period consensus was reached. The guidelines consisted of signs and symptoms for the condition, indications and contraindications for surgery, necessary blood samples and radiological examinations prior to surgery (for gallstone disease). Photographs of the condition were included in the guidelines for sinus pilonoidalis and inguinal hernia. These guidelines were implemented in the GPs electronic health record.

Standardised referral forms: Standardised referral forms were developed by specialists in gastrointestinal surgery in cooperation with GPs (Figure 2). These referral forms consisted of three parts: information needed for anaesthesia (mandatory), information needed for surgeons (mandatory) and additional information provided by the GPs. These referral forms were implemented in the GPs' electronic health records (Profdoc Winmed).

Booking of time, date and hospital for surgery: The booking system is integrated in the electronic health record (Profdoc Winmed); booking is done at the same time as referral. Patients can choose the optimal time and hospital for surgery. The system is managed by the Day Case Surgical Department. Available times and locations for surgery during a 6-month period are presented. Surgical capacity that has not been booked within two weeks of the relevant date is withdrawn and offered to patients who are not participating in the trial.

Patient information form: A patient information form (printable, integrated in the electronic health record) was prepared by a specialist in gastrointestinal surgery. The form included information about the place and time for surgery, information about the surgical procedure, and advice for the patient following surgery. Information about possible complications of surgery was also provided.

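### The cost items name no unplanned hospital contacts or acute admissions during the wait, so the saving from one-stop may be understated

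*Protocol article*

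**What the plan says.** The Abstract of the protocol article names waiting time and costs as the primary endpoints, and Outcome measures places the economic analysis under the primary outcome. Its frame is given under Cost-minimisation analysis:

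- The method: "We will use a cost-minimisation analysis in this study, since this health care intervention has a similar medical outcome for both groups".
- The viewpoint: "The analysis will have a public health provider perspective".
- The rule for leaving costs out: "Direct health care costs that are the same in both alternatives will be excluded".
- The GP side: "The costs for the GPs providing this service will include investment, support, and time costs".
- The hospital side: "Costs of traditional referral will include hospital administration, examination at the Surgical Outpatient Department (surgeon time, nurse time"), followed by staff time for treatment at the Department of Day Case Surgery, surgical slots lost to incorrect referral, and patient travel.

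The Analysis section gives a second, partly overlapping list: "cost (patient sick leave, GP examination, hospital administration, surgical outpatient examination, surgical outpatient treatment, unused surgical capacity due to incorrect referral, patient travel cost".

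The Sample size section reports a mean total wait of 241 days in the pilot data and plans for a reduction of 60 days.

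**The concern.** All three conditions can bring a patient to hospital before the planned operation, and such a visit or admission is paid for by the public provider. How long a patient is exposed to that risk depends on how long the patient waits, and shortening the wait is what one-stop is meant to do. So this cost is expected to differ by arm if the strategy works, yet it appears in neither list.

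The plan would also not pick it up elsewhere. The Discussion states that health outcomes need not be assessed because both arms receive the same day surgery, and surgery is costed only at the day case department. A control patient admitted and operated on acutely would therefore show no cost for that episode under the listed items. The cost difference and the break-even number both depend on the per-patient costs V_OS and V_TR, so the gap would reach both results of the economic analysis.

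**Working it through.** The article states no cost, cost difference or break-even number, so there is no figure to reproduce. The check has two parts: what the text implies, and an illustration on assumed values.

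**1. The lists against the exclusion rule.** Cost-minimisation analysis names GP investment, support and time; hospital administration; the outpatient examination; day surgery; unused capacity; and travel. The Analysis section adds the GP examination and sick leave. Neither has an entry for an unplanned hospital contact between referral and surgery. The rule removes only costs that are equal between arms. A cost that accrues with waiting time is not equal when waiting time differs, so by the plan's own rule it stays in.

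**2. Change in exposure.** Inputs from Sample size: mean wait 241 days, planned reduction 60 days. 60 / 241 = 24.9%. One-stop wait: 241 − 60 = 181 days.

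**3. Contacts avoided (rates are assumptions).** Let r be the share of waiting patients with an acute contact per 30 days, the same in both arms.

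- Contacts avoided per patient = r × 60 / 30 = 2r.
- r = 1%: 0.02. r = 5%: 0.10.
- If one contact costs as much as 10 to 20 clinic visits (also assumed), this is worth 0.02 × 10 = 0.2 to 0.10 × 20 = 2.0 clinic visits per patient.

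The tenfold width comes entirely from the assumed inputs.

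**4. Effect on the break-even number (values assumed).** Solving the article's cost equality gives X = (F_OS − F_TR) / (V_TR − V_OS). The printed solution has different signs, which is a separate matter. Let S = 100 units be the per-patient saving on the listed items, F_OS − F_TR = 10,000 units, and h the cost of avoided contacts that is not listed. The full saving is S + h.

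| h | Full saving | Listed items understate by | Break-even |
|---|---|---|---|
| 0 | 100 | 0 | 10,000 / 100 = 100 |
| 10 | 110 | 10 | 10,000 / 110 = 90.9 |
| 25 | 125 | 25 | 10,000 / 125 = 80 |
| 50 | 150 | 50 | 10,000 / 150 = 66.7 |

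**5. Precision.** With 60 patients per arm, expected contacts are 60 × r × 241 / 30 in controls and 60 × r × 181 / 30 in one-stop.

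- r = 1%: 4.8 against 3.6, difference 1.2. Taking counts as Poisson, its SD is √(4.8 + 3.6) = 2.9.
- r = 5%: 24.1 against 18.1, difference 6.0. SD √(24.1 + 18.1) = 6.5.

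The SD exceeds the difference in both cases, so the trial would estimate this component imprecisely.

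**The case against.** The strongest reply is that the lists are not closed. Both are introduced as what the costing will include, the article condenses a fuller protocol, and the exclusion rule itself admits any cost that differs by arm. This stands in part: it cannot be said that these contacts will be costed at zero, only that they would be if the listed items alone are used. But the article does itemise its costs, down to surgeon, nurse and anaesthetist time, so the absence of a cost tied to the other primary endpoint deserves correction.

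A second reply is that the scope was a deliberate choice, since both arms end in the same operation. That supports leaving out the operation, not what happens before it.

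A third is that the Analysis list is framed as covariates for comparing arms. This is fair; the list that governs the costing is the one under Cost-minimisation analysis, and the change belongs there.

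A reader might also infer that one-stop shifts pre-operative work-up to the GP, so that test costs are missed as well. The guidelines do cover "necessary blood samples and radiological examinations prior to surgery (for gallstone disease"), and the one-stop form demands "information needed for anaesthesia (mandatory), information needed for surgeons (mandatory) and additional information provided by the GPs". But Patients says that all participants are diagnosed by their GP, and Logistics has the GP identify them by the guidelines before consent and randomisation. Nothing says that clinic surgeons order or repeat tests for controls. The documents therefore show no difference in tests between arms.

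**Conclusion.** The point holds as a gap in the listed cost items. Under the stated perspective and exclusion rule, unplanned hospital contacts and acute admissions for the index condition belong in the comparison. If they are left out, the saving from one-stop may be understated. That direction assumes that one-stop does shorten the wait and that the risk per day of waiting is the same in both arms.

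A reader might go further and conclude that the cost difference is biased by a material amount. The documents do not support that. They give neither a rate nor a unit cost, the lists are not said to be complete, and the contacts may prove rare. The 0.02 to 0.10 contacts per patient, and their value of 0.2 to 2.0 clinic visits, rest on assumed inputs. Nor is a clinic visit the whole saving, since one-stop also avoids the travel to it.

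**What to change.** Under Cost-minimisation analysis, add one item: emergency visits and admissions for the index condition, including any acute surgery, from randomisation to surgery or end of follow-up, for every randomised patient in both arms. Carry it into V_OS and V_TR, and align the list in the Analysis section.

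Take the data from the hospital charts that Data gathering already has reviewed weekly. The check must also cover patients who never reach day surgery, as they are the ones most likely to have been treated acutely. Contacts outside the hospital's charts would be missed; say so as a limitation.

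The cost is a small extra data item and more variance in cost from rare, expensive events. Report the cost difference and the break-even number with and without the item, so that a reader can see how far a few admissions drive the result.

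For pre-operative tests, no new data collection is needed. At most, add a sentence stating that their cost is assumed equal between arms.
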